### Sample size and power calculations

Calculations regarding the needed number of participants to measure the primary outcome – smoking cessation rates – have been done to ensure the statistical significance of the results.

For the clinical pilot, accepting an alpha risk of 0.05 and a beta risk of 0.2 in a two-sided test, 45 subjects will be necessary in both the first group and second groups in order to find a statistically significant proportion difference, which is expected to be 0.2 and 0.5 in the first and second groups, respectively.

For the public pilot, accepting an alpha risk of 0.05 and a beta risk of 0.2 in a two-sided test, 489 subjects are necessary in first group and 489 in the second to find as statistically significant a proportion difference, expected to be of 0.07 in group 1 and 0.14 in group 2.

A dropout rate of 15 and 20% is anticipated for the clinical and public pilot, respectively. Although other studies using computer-tailored interventions have reported higher dropout rates, this study will consider participants who do not return for the consultation at month 6 to be failure cases. Consequently, the anticipated dropout rates include only those who withdraw for reasons other than relapse.

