## Abstract

**Background:**

Smoking cessation is the most common preventative for an array of diseases, including lung cancer and chronic obstructive pulmonary disease. Although there are many efforts advocating for smoking cessation, smoking is still highly prevalent. For instance, in the USA in 2015, 50% of all smokers attempted to quit smoking, and only 5–7% of them succeeded – with slight deviation depending on external assistance. Previous studies show that computer-tailored messages which support smoking abstinence are effective. The combination of health recommender systems and behavioral-change theories is becoming increasingly popular in computer-tailoring. The objective of this study is to evaluate patients’s smoking cessation rates by means of two randomized controlled trials using computer-tailored motivational messages. A group of 100 patients will be recruited in medical centers in Taiwan (50 patients in the intervention group, and 50 patients in the control group), and a group of 1000 patients will be recruited on-line (500 patients in the intervention group, and 500 patients in the control group). The collected data will be made available to the public in an open-source data portal.

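### The public-pilot size of 489 per group does not follow from the stated alpha, power, 7% vs 14% rates and 20% dropout

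*Protocol article*

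**What the plan says.** In the protocol article, under Sample size and power calculations, the public-pilot size is introduced with "For the public pilot, accepting an alpha risk of 0.05 and a beta risk of 0.2 in a two-sided test". The stated requirement is "489 subjects are necessary in first group and 489 in the second", for proportions "expected to be of 0.07 in group 1 and 0.14 in group 2".

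The same section adds: "A dropout rate of 15 and 20% is anticipated for the clinical and public pilot, respectively". It explains that "the anticipated dropout rates include only those who withdraw for reasons other than relapse". It does not name a formula, and it does not say whether 489 is before or after the dropout allowance.

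The abstract sets public-pilot enrolment at "500 patients in the intervention group, and 500 patients in the control group", and Table 1 agrees.

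For the clinical pilot, with 0.2 vs 0.5 and the same alpha and beta, the section states that "45 subjects will be necessary in both the first group and second groups".

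**The concern.** The section gives every input a two-proportion calculation needs, together with the result, so the figure can be checked directly. If the result does not follow from the inputs, a reader cannot tell what the pilot was designed to do: whether it has 80% power or more, and whether it tolerates 20% loss or considerably more. The second question matters here. The section itself notes that comparable studies reported higher dropout, and the Discussion (Problems anticipated) names dropout as a main challenge.

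**Working it through.** **Inputs (Sample size and power calculations):** two-sided alpha 0.05 (z = 1.960); beta 0.2 (z = 0.842); p1 = 0.07, p2 = 0.14, so difference 0.07 and mean 0.105; dropout 20%; stated n = 489 per group. Enrolment of 500 per group is from the abstract and Table 1.

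**Step 1. Evaluable number per group at 80% power.**

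- Pooled normal: n = [1.960·√(2·0.105·0.895) + 0.842·√(0.07·0.93 + 0.14·0.86)]² / 0.07² = (0.8497 + 0.3625)² / 0.0049 = 299.9, so 300.
- Arcsine: h = 2·asin√0.14 − 2·asin√0.07 = 0.2315; n = 2·(1.960 + 0.842)² / h² = 293.0, so 293.
- Continuity-corrected: n' = (299.9/4)·[1 + √(1 + 4/(299.9·0.07))]² = 327.8, so 328.
- The unpooled formula gives 297, inside this range.

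**Step 2. Add the stated 20% dropout, n/(1 − 0.20).**

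| Formula | Evaluable | With 20% dropout | Shortfall from 489 |
|---|---|---|---|
| Arcsine | 293 | 367 | 122 |
| Pooled normal | 300 | 375 | 114 |
| Continuity-corrected | 328 | 410 | 79 |

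Multiplying by 1.20 instead of dividing by 0.80 gives 352 to 394. One-sided versions are smaller still. The stated figure is not reproduced, with or without dropout.

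**Step 3. Which changes would reach about 489?**

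| Change from the stated inputs | Result |
|---|---|
| Arcsine, 80% power, 40% loss | 293/0.60 = 488.3, so 489 |
| Continuity-corrected, 80% power, 33% loss | 327.8/0.67 = 489.3 |
| Arcsine, 90% power, stated 20% loss | 392.2/0.80 = 490.3 |
| Pooled, 80% power, stated 20% loss, 0.07 vs 0.13 | 391.3/0.80 = 489.1 |

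**Step 4. Cross-check on the clinical pilot (0.2 vs 0.5, 15% dropout, stated 45).** Arcsine gives 37.9, so 38; 38/0.85 = 44.7, so 45. The continuity-corrected formula with no dropout gives 44.9, also 45. The pooled formula gives 39, and 39/0.85 = 45.9, so 46. The clinical figure is therefore compatible with its inputs, but it does not identify one formula.

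**Step 5. Power under the stated rates,** pooled normal: Φ{[0.07·√n − 0.8497] / √0.1855}.

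- 489 evaluable: 94.8%.
- 391 evaluable (489 less 20%): 89.3%.
- 400 evaluable (500 less 20%): 89.9%.
- 300 evaluable (500 less 40%): 80.0%.

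**The case against.** The strongest reply is that nothing is lost. Under the stated rates the discrepancy is on the safe side: 500 enrolled per group keeps about 90% power after 20% loss, and no analysis or recruitment target depends on 489. That stands, and it limits the point to a reporting correction. It does not make the stated figure right.

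Three stronger readings are tempting, and the document does not support them.

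- **That 40% dropout was the true input.** The arcsine formula with 40% loss gives exactly 489, and with the stated 15% it gives the clinical 45, so this is a plausible origin. But no formula is named, 40% appears nowhere as a dropout figure, the clinical 45 has a second derivation, and the other routes in step 3 come equally close. One of them leaves alpha, power and dropout untouched and moves a single rate by one percentage point.
- **That the pilot misses its own target.** If 489 is the evaluable requirement, 500 less 20% leaves 400, which is below 489. But 400 is well above the 293 to 328 that the stated inputs require, so the shortfall is only against a figure that cannot be reproduced.
- **That inflating for dropout is wrong because non-returners count as failures.** The section says that "the anticipated dropout rates include only those who withdraw for reasons other than relapse". On that wording the 20% can be read as losses additional to those counted as failures, and inflating the sample for them is defensible.

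**Conclusion.** The figure is wrong as written. With two-sided alpha 0.05, 80% power and 0.07 vs 0.14, the requirement is 293 to 328 evaluable per group, or 367 to 410 with 20% dropout. The stated 489 exceeds this by 79 to 122 per group. This holds for the arcsine, pooled, unpooled and continuity-corrected formulas, so it does not rest on a choice of method.

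Either the power, the dropout or an expected rate is misreported, or 489 is itself an error; the cause cannot be settled from the document. Under the stated rates the effect is oversizing, with power of about 89–90% after 20% loss against the 80% claimed. That power figure assumes that 0.07 and 0.14 are the intended rates. If the design rate was really 0.13, 489 enrolled with 20% loss would give about the stated 80%.

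**What to change.** Trace the original calculation and do one of the following.

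- Correct whichever of power, dropout or expected rate was misreported, so that 489 follows from the text.
- Keep the stated inputs and restate the paragraph along these lines: about 300 per group gives 80% power for 7% vs 14% (375 with 20% dropout); the planned 500 per group gives about 90% power at 20% loss and 80% at 40% loss.

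In either case, name the formula and say, for both pilots, whether the stated number already includes dropout. This is a change of text only; enrolment of 500 per group stays as planned.

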### Planned recruitment rate

The clinical pilot recruitment rate is expected to be 17 per month in average, with the exception of February 2018 in which we do not expect to have recruit patients due the Chinese new year festivities. In the public pilot, we the planned recruitment rate is 700 users in the first 4 months, and 300 users in the three remaining months. This difference in the rate is due to the fact that we plan to conduct a digital marketing campaign to promote the app in the first 4 months, and that we expect a reduced number of new users in February coinciding with the Chinese new year. Figure 1 summarizes the difference in the recruitment, execution, and assessment periods for both pilots, and Fig. 2 details it.

**Fig. 1 Fig1:**
[figure not shown]
Difference of enrollment, intervention, and assessments periods in the clinical and public pilots

**Fig. 2 Fig2:**
[figure not shown]
Standard Protocol Items: Recommendations for Interventional Trials (SPIRIT) Schedule of enrollment, interventions, and assessments

### Materials

The clinical pilot will make use of all the materials normally used to treat patients at the smoking cessation units at Taipei Welcome Clinic and Taipei Medical University Hospital.

Carbon monoxide levels will be tested using a PiCO Smokerlyzer CO-oximeter; a value range of 0–6 will be considered normal for a non-smoker. Similarly, a Safecare Biotech COT Rapid Test device, which contains line indicators for positive and negative test results, will be used to measure urinary cotinine levels.

Several smoking cessation medications will be used during the trial: Nicotinell TTS 20 and TTS 30 patches, Nicotinell 2-mg chewing gum and 10-mg inhalers, Buporin 150-mg sustained-release tablets, and Champix 0.5-mg and 1-mg tablets. The dosage and duration of each medication will be prescribed by the physician, and the patients will be charged NT$200 per consultation.

In addition, our specially designed mobile app will be used to deliver motivational health messages. Figure 3 shows its interface in both English and Mandarin. The app has been programmed in Android’s native language. It uses Mirth Connect as its communication channel [39], Firebase for platform notifications, and PostgreSQL as its database management system.

**Fig. 3 Fig3:**
[figure not shown]
Screenshots of the app (English and Mandarin versions) showing different sections

A nurse will provide patients with instructions for downloading and using the app. Questions related to the patient’s basic demographic information and an extended profile (including social influences, plan of action, skills, attitudes, and self-efficacy with regard to smoking) will be assessed in the app.

The data obtained from the database will be analyzed in a comma-separated value (CSV) format using SPSS software.

Users’ physical activity data will be collected using their mobile phones. The mobile app will use GoogleFit [40] to track daily physical activity. These data will be available to users through the GoogleFit app but not displayed within the 3M4Chan app, as it will be utilized for research purposes only.

Patients will be followed up after 60, 120, and 180 days of their initial consultation with a variance margin of 5 days. In the initial consultation, the patient will be assessed in the smoking cessation unit after they have been referred from either the pneumology unit or another clinical department. Smoking-related symptoms, treatment adherence, daily cigarette use, and possible adverse events will be discussed and exhaled carbon monoxide, urinary cotinine, and other clinical information, such as weight and height, will be assessed. Quality of life (EQ-5D-5 L, IPAQ, and SF-36) questionnaires will also be collected. The patient will be instructed on relaxation techniques and on tips to avoid smoking.

During the second consultation, physicians will gather patient information on smoking-related symptoms, treatment adherence, daily cigarette use, possible adverse events, exhaled carbon monoxide and urinary cotinine levels, and other clinical information. Coaching for relapse prevention will be performed.

At the third consultation, information about smoking-related symptoms, treatment adherence, possible adverse events, exhaled carbon monoxide and urinary cotinine levels, and other clinical information will again be collected. New relaxation techniques will be explained if the previously taught techniques have not been effective. Techniques for relapse prevention will be reviewed. It will also be collected the users’ physical and psychological health state, their exhaled carbon monoxide levels, the results from a urinary cotinine test, and will be asked clinical information such as weight and height.

At the fourth consultation, physicians will collect information about smoking-related symptoms, treatment adherence, and possible adverse events. Techniques for avoiding the risk of relapse are reinforced. Data about blood pressure, weight, height, and quality of life (using EQ-5D-5 L, IPAQ, and SF-36 questionnaires as well as a questionnaire assessing the satisfaction about the motivational messages received through the 3M4Chan app) will also be collected. All input clinical data will be checked for correctness by two healthcare professionals to ensure quality.

The public pilot will use the same mobile app as the clinical pilot. No additional materials will be used.

## Discussion

### Expected outputs for validation of our hypothesis

Recently, several recommender systems have been implemented to support smoking cessation [33, 41, 42]. We expect that our recommender-system-aided motivational messages will help increase user engagement at both the individual and aggregate level and lead to prolonged periods of smoking abstinence in accordance with our hypothesis. This will be validated by the metrics measured over the course of our study, such as the health recommender system precision, smoking abstinence, app usage statistics, and user feedback.

### Expected outcomes

We hope to provide a new method to achieve smoking cessation that will be integrated into the usual care received by patients. This can either come from just using the mobile app in the public intervention, or by combining the mobile app with the pharmacological treatment in the clinical intervention setting. Despite being different approaches, achieving an increase to smoking cessation rates will help to reduce the incidence of diseases directly related to smoking as well as those arising from exposure to secondhand smoke. This will lead to increased life expectancy and improved life quality.

### Dissemination of the results

The results of this study will be published, and a subset of the retrieved data will be made public as part of the SmokeFreeBrain project’s database. Public datasets will be fully anonymized and protected in accordance with directives 2002/58/EC [43] and 95/46/EC [44], which regulate the protection of privacy in electronic communications and the processing and free movement of personal data.

The data will be made available through an open-source data management portal based on CKAN. Third-party researchers and organizations will have access to both the raw data (where anonymization has made this possible) and to a rich set of metadata for each dataset. In this portal, users will be able to search up to field level different keywords and tags to browse related datasets, and see their format, availability, and licensing type. The published datasets will be a valuable resource for future studies, and we intend this portal become a base reference point for future related studies.

### Problems anticipated

The dropout rate among participants is one of the main challenges we anticipate for this study. Patients might dropout by ceasing to share EHR data, by terminating their use of the app, or by becoming unresponsive to follow-ups over the course of the trial.

### Ethics

This study has been approved by the Ethical Committee of Taipei Medical University-Joint Institutional Review Board (TMU-JIRB) and has been registered at ClinicalTrials.gov with ID: NCT03108651. The study includes all items from the World Health Organization Trial Registration Dataset (Additional file 3).

### Informed consent

Patients in the clinical pilot will sign an informed consent. All patients using the app, regardless of which pilot they are participating in, will be asked to read and accept the terms and conditions (http://13.114.86.199/policy-en.html), which explain the usage of their data and app analytics, the rights they have during the pilot, and the offered services by the pilot 3M4Chan app in detail.

### Trial status

Currently recruiting.

## Abbreviations

3M4Chan: Mobile Motivational Messages for Change
App: Mobile application
EHR: Electronic Health Record
QALYs: Quality-adjusted life years
RCT: Randomized controlled trial
SFB: SmokeFreeBrain
SoLoMo: Social, Local, and Mobile
